## Abstract

Background

Anemia is characterized by a lower red blood cell (RBC) count than the usual rate or the average count that should be found in the blood. It is described by the reduction in the concentration of hemoglobin, the number of RBCs, and the O2-carrying capacity of the blood. A complete blood count (CBC) gives serious information on changes in the size and shape of RBCs and an indication of inclusion bodies that will help exclude anemia. RBC indices suggest potential reasons for the anemia in a particular patient. Thus, RBC indices can give some clues about the possible cause of anemia in a given patient with the disease. It is also necessary to look at the peripheral blood smear (PBS) and RBC indices and histogram to evaluate anemia adequately.

Method

The primary complaints of volunteers, such as clinical anemia as well as essential family medical history, will be the criteria for selection. After that, the main procedures that will be performed are the PBS and CBC. The blood sample will be drawn while the individual sits securely and in an aseptic setting. An ethylenediaminetetraacetic acid (EDTA) tube will be used to collect 2 ml of venous blood, which will then be gently mixed and processed on a five-part automated hematology analyzer (Coulter) for CBC test and PBS.

Expected results

The diagnostic capabilities of the PBS procedure are expected to match with RBC histograms and indices in the CBC report for the detection of anemia. Comparing both results with the PBS evaluated at the microscopic assessment, it is expected to likely provide a more precise and quantifiable result on RBC morphology and indices with greater accuracy for anemia detection in accordance with the PBS report. Implementing RBC histogram analysis in routine clinical practice is expected to enhance the diagnostic processes for anemia, leading to a more effective and timelier patient treatment.

Conclusion

These findings will suggest that applying RBC histograms and indices in CBC reports in supportive diagnosis with PBS analysis in the everyday clinical practice of hematology may improve the diagnoses and overall care of patients with anemia. Advanced research should confirm the efficacy of integrated approaches to increase diagnostic accuracy.

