## Materials and methods

Study design* *

This cross-sectional study was carried out in the Central Laboratory Department of Pathology at Acharya Vinoba Bhave Rural Hospital, affiliated with Datta Meghe Institute of Higher Education and Research (Deemed to be a University), located in Sawangi, Wardha, Maharashtra, India. The study commenced following the receipt of participants' consent and has been approved by the Institutional Ethics Committee of Datta Meghe Institute of Higher Education and Research (approval number: DMIHER (DU)/IEC/2024/157). It was also registered with the Clinical Trials Registry of India (CTRI/2024/04/066473) (Appendices). A minimum of 314 eligible participants were involved, and the study spanned one year to ensure comprehensive data collection.

Participants

Patients of Indian origin aged 11-65 years diagnosed with anemia will be included. Exclusion criteria include patients diagnosed with leukemia, lymphoma, or other blood disorders as well as those under 11 or over 65 years of age. Patients with chronic kidney disease and liver disease will be excluded as these diseases affect the production of RBS and the indices of erythropoiesis. Patients who are on chronic medications which are known to alter the morphology of RBCs including chemotherapy will also be excluded. Those patients, who were transfused with blood within the last three months, will be excluded from the study since it may shift their RBC parameters slightly.

Data collection procedure

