Both the benefits and drawbacks of their participation will be discussed with the participants. To avoid any misunderstandings, participants will be given written information about the consent before their enrolment. Potential volunteers will be chosen based on their primary complaints such as clinical anemia and family history. The blood sample will be drawn while the individual sits securely and in an aseptic setting. Two milliliters of venous blood will be collected in an ethylenediaminetetraacetic acid (EDTA) tube, gently mixed, and processed using a five-part automated hematology analyzer (Coulter) for complete blood count (CBC) testing and the estimation of RBC indices, including MCV, MCH, MCHC, and RDW. Based on various RBC indices and a histogram, the Beckman counter-analysis report will be examined to diagnose the kind of anemia. Simultaneously, a blood smear will be prepared in a Blue Star slide (75 mm length, 25 mm width, 1.35 mm thickness) from the given blood sample and allowed to dry. After that, staining will be performed using Leishman's stain and Leishman's buffer. The smear will next be examined under a microscope with an oil immersion lens (100×), and the findings will be recorded to make the morphological diagnosis of anemia. One pathologist will independently perform the morphological analysis to ensure accuracy and consistency. The PBS and cell counter methods will be used to collect the data, and the data will be compared and analyzed by using tests like the paired t-test and chi-squared test to draw a conclusion.

CBC

After the blood sample is collected in the EDTA tube, it will be sent to the pathology processing lab. The sample will be aligned in a cassette for processing. Then the cassette will be kept in the Beckman Coulter B1 (UniCel DxH 800). By using the principle of electrical impedance, results will be given by the machine, and this result will be used to analyze CBC and its relation with anemia. Based on various RBC indices and a histogram, the Beckman counter-analysis report will be examined to diagnose the kind of anemia.

PBS

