PBS provides valuable information for diagnosing anemia by examining minute variations in the morphology of blood cells. The procedure is as follows: A small layer of blood will form on the smear. After allowing it to air-dry, place them on a dyeing rack. After pouring Leishman's dye drop by drop on the slide, set it for two minutes. This makes it possible to calculate peripheral blood film (PBF) in methyl alcohol. After pouring twice as much buffering water on the slide by drops, let it rest for eight minutes before washing it for a minute or two. After allowing it to air-dry, examine it using a microscope's oil immersion lens. After that, the smear will be examined under a microscope with an oil immersion lens (100×) to determine the morphological diagnosis of anemia, and the results will be recorded. Abnormalities in the size, shape, or color of RBCs (anisocytosis, poikilocytosis, hypochromia) are valuable assets in the distinction between the various types of anemia.

Sample size

The sample size was calculated using Cochran's formula by considering the proportion of the estimated prevalence of anemia (p=28.6%) from the reference article and the estimation error (d = 5%); hence, calculating the total number of anemic patients visiting the hospital, the population size (N) of 314 patients is needed in the study.

The sample size for this study was determined using Cochran's formula. The formula used is as follows: n>=𝑍²1-𝛼/₂×(1−𝑝)/E2. Here, 𝑍²1-𝛼/₂ is the level of significance at 5%, i.e., confidence interval is equal to 1.96, p is equal to 28.6% or 0.286, and E (error of margin) is equal to 5% or 0.05. Thus, n>=1.96^2^×0.286×(1−0.286)/(0.05)², resulting in 313.7 or 314 patients needed in the study [14].

Outcome measures

Under a microscope, we will examine the RBCs in anemic patients for abnormalities such as variations in size, shape, and color, which are indicative of different types of anemia. However, CBC, which reports the amount of Hb in the blood, is always helpful for diagnosing anemia.

Statistical analysis

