The complete analysis dataset will consist of all the anemic patients with no missing values for any parameters in the dataset. The primary variables include MCHC, MCV, RDW, and MCHC. All the data will be summarized for the PBS and automated hematology analyzer results of the anemic patients. Demographic variables will be presented using frequencies and percentages for categorical data and means and standard deviations for continuous data. Outcome variables for continuous data will be analyzed and summarized with maximum, mean, minimum, standard deviation, standard error, and a 95% confidence interval for parametric data. Continuous outcome variables will first be tested for normality using the Kolmogorov-Smirnov test at a 5% significance level (p≤0.05). To compare the results of CBC and PBF methods, data will be evaluated finding the sensitivity, specificity, positive predictive value (PPV), negative predictive value (NPV), and accuracy for both methods. If the data is normally distributed, a paired t-test will compare the means of related groups (CBC group with positive and negative cases). If the data is not normally distributed, the Mann-Whitney test will be used. However, the PBS group with positive and negative cases will be evaluated using the chi-squared test or McNemar's test. This analysis will determine the more effective diagnostic method.

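### The abstract promises accuracy for detecting anemia, but every analysed patient is anemic; the planned measures can be estimated only for the type of anemia, and the Statistical analysis section does not say so

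*Protocol article*

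**What the plan says.** The abstract (Expected results) frames the result as detection twice. PBS is expected to match "RBC histograms and indices in the CBC report for the detection of anemia", and the comparison is expected to be more precise, "with greater accuracy for anemia detection in accordance with the PBS report".

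The population is anemic by definition. Under Participants: "Patients of Indian origin aged 11-65 years diagnosed with anemia will be included". Under Statistical analysis: "The complete analysis dataset will consist of all the anemic patients with no missing values for any parameters in the dataset". The Sample size section also describes the 314 as anemic patients. No non-anemic group is described anywhere.

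Under Statistical analysis, "data will be evaluated finding the sensitivity, specificity, positive predictive value (PPV), negative predictive value (NPV), and accuracy for both methods". Table 1 lists the same measures. Positive and negative cases are mentioned for each method without saying what either is positive for.

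Other sections give a different target. The Data collection procedure uses the analyzer report to decide the kind of anemia and the smear for a morphological diagnosis. Outcome measures refers to smear abnormalities that point to different types. The Results section asks whether the histogram can identify microcytic, macrocytic and normocytic anemia, with PBS as comparator.

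**The concern.** Specificity and NPV need people without the target condition. If the condition is anemia, the analysis set contains none, so the abstract's claim cannot be tested on the data to be collected.

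The Statistical analysis section says the comparison will settle which method is more effective. If positive were coded as anemia found, four of the five measures in Table 1 would be undefined, fixed by design or a repeat of sensitivity. The text does not rule that coding out: the abstract suggests it, and the section that fixes the measures never links them to the three types named under Results.

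**Working it through.** **Inputs.** N = 314, all anemic (Sample size; Participants; Statistical analysis). Non-anemic patients: 0.

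**The plan's own figure.** Cochran's formula with p = 0.286, E = 0.05 and z = 1.96:

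n = 1.96² × 0.286 × 0.714 / 0.05² = 313.79, rounded up to 314.

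The stated sample size is reproduced. The argument below needs only that all 314 are anemic.

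**Target 1: anemia present or absent.** With no non-anemic patients, false positives (FP) = true negatives (TN) = 0 whatever the method does. Hence:

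- specificity = TN/(TN + FP) = 0/0
- PPV = TP/(TP + FP) = TP/TP = 100% whenever TP > 0
- NPV = TN/(TN + FN) = 0/FN = 0% if any case is missed, and 0/0 if none is missed
- accuracy = (TP + TN)/314 = TP/314 = sensitivity

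For a range of assumed sensitivities:

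| Assumed sensitivity | TP | FN | Specificity | PPV | NPV | Accuracy |
|---|---|---|---|---|---|---|
| 0.70 | 220 | 94 | 0/0 | 100% | 0% | 70.1% |
| 0.80 | 251 | 63 | 0/0 | 100% | 0% | 79.9% |
| 0.90 | 283 | 31 | 0/0 | 100% | 0% | 90.1% |
| 1.00 | 314 | 0 | 0/0 | 100% | 0/0 | 100% |

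Accuracy differs from the first column only because TP is rounded to whole patients. The last row is also the score of a method that calls every sample positive unseen.

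**Target 2: one morphological type against the rest, PBS as reference.** Patients whose smear shows another type are now the negatives. The article gives no type shares, so those below are assumptions. Half-widths are 1.96 × √(0.9 × 0.1/n), for an assumed true value of 90%.

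| Assumed share of the type | Positives | Negatives | Half-width, sensitivity | Half-width, specificity |
|---|---|---|---|---|
| 50% | 157 | 157 | 4.7 points | 4.7 points |
| 30% | 94 | 220 | 6.1 points | 4.0 points |
| 10% | 31 | 283 | 10.6 points | 3.5 points |

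Both rows of the 2x2 table are filled, so all five measures can be estimated from the same 314 patients. What decides whether they carry information is the definition of positive and negative, which the Statistical analysis section does not give.

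**The case against.** The strongest reply is that typing is the operative aim and the abstract is loosely worded. Data collection procedure, Outcome measures and Results all point to typing, and for typing an anemic-only sample is appropriate. This stands. A reader might infer that the whole accuracy table is void or that empty measures will be published. The documents support neither: the table fails only under the detection reading.

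A second reply is that the coding of positive and negative may be left to an analysis plan that is not shown. That is fair for the detail. It does not remove the conflict between the stated claim, the eligibility rule and the analysis set, all of which are printed in the article.

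A third is that anemic patients with an unremarkable smear could serve as PBS negatives. A specificity could then be calculated, but those patients are still anemic, so it would not be specificity for anemia.

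Two further inferences are tempting and should not be drawn.

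- **That the complete blood count (CBC) is positive in everyone by entry.** Outcome measures says only that "CBC, which reports the amount of Hb in the blood, is always helpful for diagnosing anemia", and Participants does not say how anemia is established for entry. The Introduction describes anemia as diagnosed on the smear. Table 1 rates the histogram rather than hemoglobin, and normocytic anemia has a mean cell volume in the usual range.
- **That non-anemic volunteers are tested and then discarded.** The Data collection procedure says "Potential volunteers will be chosen based on their primary complaints such as clinical anemia and family history", but nowhere is it said that non-anemic people are tested and dropped. As diagnosed anemia is an inclusion criterion, the diagnosis may come before sampling.

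**Conclusion.** The concern holds, limited to the detection target. Given the stated eligibility and analysis set, detection specificity is 0/0, PPV is 100% by construction, NPV is 0% or undefined, and accuracy equals sensitivity. These results follow from having no non-anemic patients and do not depend on 314 or on any assumed sensitivity; PPV needs only one patient called positive. The study cannot support the detection statements in the abstract.

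It does not follow that the design or the choice of measures is wrong. For typing against PBS, all five measures can be estimated; only the precision figures above rest on assumed type shares and an assumed 90%. The defect is that the abstract names a target the data cannot address, while the Statistical analysis section does not tie its positive and negative cases to the target the data can address.

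**What to change.** 1. In the abstract's expected results, remove both references to detecting anemia and describe the expected result as agreement on, or accuracy for, the morphological type.
2. In the Statistical analysis section, add a definition such as: *Among anemic patients, the sensitivity, specificity, PPV, NPV and accuracy of the histogram and indices will be computed separately for microcytic, macrocytic and normocytic anemia, each against the other types combined, with PBS as the reference. A negative is a patient of another type, never a patient without anemia.*

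The cost is two wording changes in the abstract and a short definition in the methods, with no additional patients, samples or tests. The downside is that the study gives up the detection claim. Keeping that claim would take more than wording: it would need non-anemic participants and a reference standard for anemia independent of the methods compared, and the article describes neither.

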## Introduction

Based on the study across the world, 40% of children aged 6-59 months, 37% of pregnant women, and 30% of women in the age group of 15-49 years suffer from anemia [1]. By using the WHO criteria, severe anemia refers to hemoglobin (Hb) levels less than 70 g/L among children aged below five years and less than 80 g/L among other age groups [2]. This ensures that treatment is tailored to address the root cause, whether it be nutritional deficiencies, chronic diseases, or genetic disorders, leading to better patient outcomes. Abnormalities in the size, shape, or color of red blood cells (RBCs) (anisocytosis, poikilocytosis, hypochromia) are valuable assets in the distinction between the various types of anemia. For example, microcytic and hypochromic RBCs are characteristics of iron deficiency anemia, while macrocytic RBCs may suggest malnutrition and vitamin B12 or folate deficiency [3].

Anemia is diagnosed using the peripheral blood smear (PBS), where a microscopic analysis of the blood smear provides valuable knowledge about the variation of the shape and size of RBCs or the presence of any inclusion bodies. Microscopic examination can show an abnormality in the size and shape of RBCs when analyzing a smear of the peripheral blood to identify anemia [4]. Morphologically, anemia can be categorized using RBC indices [5]. RBC indices derived from RBC and Hb analysis are essential in determining the underlying cause of anemia. Using such indices, it also becomes possible to distinguish between microcytic, macrocytic, or normocytic anemia [6]. RBC indices measure the size and concentration of Hb in RBCs. Irregular results affect the type and concentration of anemia [7]. The mean corpuscular volume (MCV) is the sample's average quantity of all the counted RBCs. The value is expressed in terms of femtoliters (fL), a volume unit of measurement, and it typically ranges from 80 to 100. The mean weight of Hb per cell is known as the mean corpuscular hemoglobin (MCH). It usually ranges from 27 to 33 picograms. The mean corpuscular hemoglobin concentration (MCHC) represents the average weight of Hb per cell relative to its volume. It typically has a value of 32-36 g/dL [8].

When an erythrocyte's average size is lower than usual, it is known as microcytic anemia (MCV <80 fL). Generally observed in long-term iron deficiency anemia, a variety of conditions can induce macrocytic anemia, a deficiency of vitamin B12, which is characterized by a mean RBC volume that is more than usual (MCV >100 fL). Normocytic anemia is defined as anemia with a low blood count but an MCV in a typical range of 80-100 fL. It can be caused by hemolytic anemia, dietary deficiencies, or renal failure [9].

An automated hematology analyzer produces a graphical representation known as an RBC histogram. It is a standard part of a complete blood picture, which supplies clues in the diagnosis of various RBC disorders and gives valuable data regarding RBC parameters like red blood cell distribution width (RDW), MCH, and MCV [10,11]. The graphical representation of cell frequencies versus size is called a histogram. A cell's size is displayed on the x-axis, while the overall number of cells is displayed on the y-axis. They provide crucial guidance for diagnosing and managing severe disorders affecting RBC [12]. PBS examination, RBC histograms, and RBC indices are essential tools for accurately diagnosing and classifying anemia [13].

## Materials and methods

Study design* *

This cross-sectional study was carried out in the Central Laboratory Department of Pathology at Acharya Vinoba Bhave Rural Hospital, affiliated with Datta Meghe Institute of Higher Education and Research (Deemed to be a University), located in Sawangi, Wardha, Maharashtra, India. The study commenced following the receipt of participants' consent and has been approved by the Institutional Ethics Committee of Datta Meghe Institute of Higher Education and Research (approval number: DMIHER (DU)/IEC/2024/157). It was also registered with the Clinical Trials Registry of India (CTRI/2024/04/066473) (Appendices). A minimum of 314 eligible participants were involved, and the study spanned one year to ensure comprehensive data collection.

Participants

Patients of Indian origin aged 11-65 years diagnosed with anemia will be included. Exclusion criteria include patients diagnosed with leukemia, lymphoma, or other blood disorders as well as those under 11 or over 65 years of age. Patients with chronic kidney disease and liver disease will be excluded as these diseases affect the production of RBS and the indices of erythropoiesis. Patients who are on chronic medications which are known to alter the morphology of RBCs including chemotherapy will also be excluded. Those patients, who were transfused with blood within the last three months, will be excluded from the study since it may shift their RBC parameters slightly.

Data collection procedure

Both the benefits and drawbacks of their participation will be discussed with the participants. To avoid any misunderstandings, participants will be given written information about the consent before their enrolment. Potential volunteers will be chosen based on their primary complaints such as clinical anemia and family history. The blood sample will be drawn while the individual sits securely and in an aseptic setting. Two milliliters of venous blood will be collected in an ethylenediaminetetraacetic acid (EDTA) tube, gently mixed, and processed using a five-part automated hematology analyzer (Coulter) for complete blood count (CBC) testing and the estimation of RBC indices, including MCV, MCH, MCHC, and RDW. Based on various RBC indices and a histogram, the Beckman counter-analysis report will be examined to diagnose the kind of anemia. Simultaneously, a blood smear will be prepared in a Blue Star slide (75 mm length, 25 mm width, 1.35 mm thickness) from the given blood sample and allowed to dry. After that, staining will be performed using Leishman's stain and Leishman's buffer. The smear will next be examined under a microscope with an oil immersion lens (100×), and the findings will be recorded to make the morphological diagnosis of anemia. One pathologist will independently perform the morphological analysis to ensure accuracy and consistency. The PBS and cell counter methods will be used to collect the data, and the data will be compared and analyzed by using tests like the paired t-test and chi-squared test to draw a conclusion.

CBC

After the blood sample is collected in the EDTA tube, it will be sent to the pathology processing lab. The sample will be aligned in a cassette for processing. Then the cassette will be kept in the Beckman Coulter B1 (UniCel DxH 800). By using the principle of electrical impedance, results will be given by the machine, and this result will be used to analyze CBC and its relation with anemia. Based on various RBC indices and a histogram, the Beckman counter-analysis report will be examined to diagnose the kind of anemia.

PBS

PBS provides valuable information for diagnosing anemia by examining minute variations in the morphology of blood cells. The procedure is as follows: A small layer of blood will form on the smear. After allowing it to air-dry, place them on a dyeing rack. After pouring Leishman's dye drop by drop on the slide, set it for two minutes. This makes it possible to calculate peripheral blood film (PBF) in methyl alcohol. After pouring twice as much buffering water on the slide by drops, let it rest for eight minutes before washing it for a minute or two. After allowing it to air-dry, examine it using a microscope's oil immersion lens. After that, the smear will be examined under a microscope with an oil immersion lens (100×) to determine the morphological diagnosis of anemia, and the results will be recorded. Abnormalities in the size, shape, or color of RBCs (anisocytosis, poikilocytosis, hypochromia) are valuable assets in the distinction between the various types of anemia.

Sample size

The sample size was calculated using Cochran's formula by considering the proportion of the estimated prevalence of anemia (p=28.6%) from the reference article and the estimation error (d = 5%); hence, calculating the total number of anemic patients visiting the hospital, the population size (N) of 314 patients is needed in the study.

The sample size for this study was determined using Cochran's formula. The formula used is as follows: n>=𝑍²1-𝛼/₂×(1−𝑝)/E2. Here, 𝑍²1-𝛼/₂ is the level of significance at 5%, i.e., confidence interval is equal to 1.96, p is equal to 28.6% or 0.286, and E (error of margin) is equal to 5% or 0.05. Thus, n>=1.96^2^×0.286×(1−0.286)/(0.05)², resulting in 313.7 or 314 patients needed in the study [14].

Outcome measures

Under a microscope, we will examine the RBCs in anemic patients for abnormalities such as variations in size, shape, and color, which are indicative of different types of anemia. However, CBC, which reports the amount of Hb in the blood, is always helpful for diagnosing anemia.

Statistical analysis

The complete analysis dataset will consist of all the anemic patients with no missing values for any parameters in the dataset. The primary variables include MCHC, MCV, RDW, and MCHC. All the data will be summarized for the PBS and automated hematology analyzer results of the anemic patients. Demographic variables will be presented using frequencies and percentages for categorical data and means and standard deviations for continuous data. Outcome variables for continuous data will be analyzed and summarized with maximum, mean, minimum, standard deviation, standard error, and a 95% confidence interval for parametric data. Continuous outcome variables will first be tested for normality using the Kolmogorov-Smirnov test at a 5% significance level (p≤0.05). To compare the results of CBC and PBF methods, data will be evaluated finding the sensitivity, specificity, positive predictive value (PPV), negative predictive value (NPV), and accuracy for both methods. If the data is normally distributed, a paired t-test will compare the means of related groups (CBC group with positive and negative cases). If the data is not normally distributed, the Mann-Whitney test will be used. However, the PBS group with positive and negative cases will be evaluated using the chi-squared test or McNemar's test. This analysis will determine the more effective diagnostic method.

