## Results

This study therefore seeks to determine whether an RBC histogram can diagnose the three types of anemia, microcytic, macrocytic, and normocytic [15], with reference to the traditional method of diagnosing the condition using the PBS examination. This study will determine the efficiency of RBC histogram analysis by comparing the diagnostic findings with that of PBS examination which will be used. Thus, the use of this approach will offer the researcher an understanding of how efficient RBC histogram analysis is as compared to the PBS examination in the identification of diverse types of anemia. Better results in diagnostic capabilities are expected, with RBC histograms likely providing more precise and quantifiable data on RBC indices. Implementing RBC histogram analysis in routine clinical practice is expected to enhance diagnostic processes for anemia, leading to a more effective and timelier patient treatment.

Table 1 shows the metric table to compare the RBC histogram and PBS.

**Table 1 TAB1:** Metric table to compare the RBC histogram and PBS RBC: red blood cell; PBS: peripheral blood smear; PPV: positive predictive value; NPV: negative predictive value

Metric	RBC histogram	PBS
Sensitivity		
Specificity		
PPV		
NPV		
Diagnostic efficiency (overall accuracy)		
Time per sample		
Cost per test		

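### With only anemic patients enrolled, the study cannot support a claim about detecting anemia; classification by type can be estimated, but positive and negative are not defined for it

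*Protocol article*

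**What the plan says.** **Who is studied.** Under Participants: "Patients of Indian origin aged 11-65 years diagnosed with anemia will be included". Under Data collection procedure: "Potential volunteers will be chosen based on their primary complaints such as clinical anemia and family history". Under Statistical analysis: "The complete analysis dataset will consist of all the anemic patients with no missing values for any parameters in the dataset". No non-anemic or control group is described anywhere in the article.

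**What is claimed.** Expected results in the abstract speaks twice of detecting anemia, the second time as "greater accuracy for anemia detection in accordance with the PBS report".

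**What is calculated.** Under Statistical analysis, "data will be evaluated finding the sensitivity, specificity, positive predictive value (PPV), negative predictive value (NPV), and accuracy for both methods". The same paragraph refers to a "CBC group with positive and negative cases" and to a PBS group split in the same way, and says the analysis will show which method is more effective. Table 1 has one row for each accuracy metric, with one column for the RBC histogram and one for PBS.

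**What the aim is.** Results says the study seeks to "determine whether an RBC histogram can diagnose the three types of anemia, microcytic, macrocytic, and normocytic", with PBS examination as the reference. Data collection procedure likewise says the analyzer report is read to find the kind of anemia.

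**The concern.** The article points to two target conditions. One is anemia itself (abstract). The other is the type of anemia among people who have it (Results). The enrolled population fits only the second.

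If the planned metrics are read as concerning anemia itself, false positives cannot occur. A reader of the abstract could then take high PPV and accuracy as evidence that histograms and indices detect anemia, when those values follow from who was enrolled.

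If they are read as concerning type, the metrics are meaningful, but three types give three sets of them. Table 1 has room for one set per method, and no text says which type, or which pooling rule, fills it. If that is chosen after the data are seen, the choice could affect which method is called the more effective.

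**Working it through.** **Inputs.** From the article: at least 314 participants, all anemic; z = 1.96; p = 0.286; E = 0.05; five accuracy metrics; three types; PBS as reference. The article does not give the share of each type or an expected specificity or sensitivity, so those below are assumptions.

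**1. The plan's own figure.** n = z² × p × (1 − p) / E² = 1.96² × 0.286 × 0.714 / 0.05² = 313.79, rounded up to 314. The stated size is reproduced.

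**2. Target = anemia present or absent.** All 314 are reference-positive, so TN = FP = 0 and TP + FN = 314.

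- Sensitivity = TP / 314
- Specificity = TN / (TN + FP) = 0/0, not estimable
- PPV = TP / (TP + FP) = TP / TP = 100%, whenever any test is positive
- NPV = TN / (TN + FN) = 0 / FN = 0, or 0/0 if no test is negative
- Accuracy = (TP + TN) / 314 = TP / 314 = sensitivity

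Two illustrations, with assumed counts:

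| Method | Sensitivity | Specificity | PPV | NPV | Accuracy |
|---|---|---|---|---|---|
| Calls all 314 positive | 314/314 = 100% | 0/0 | 100% | 0/0 | 100% |
| Misses 31 | 283/314 = 90.1% | 0/0 | 283/283 = 100% | 0/31 = 0 | 90.1% |

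A rule that calls everyone anemic scores perfectly on every metric that is defined. Only sensitivity carries information.

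**3. Target = one type against the other types, among the 314.** Negatives now exist. The half-width of a 95% Wald interval is 1.96 × √(0.9 × 0.1 / n). It is shown for an assumed specificity of 0.90 (n = negatives) and an assumed sensitivity of 0.90 (n = positives).

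| Assumed share of the type | Positives | Negatives | Half-width, specificity (points) | Half-width, sensitivity (points) |
|---|---|---|---|---|
| 5% | 16 | 298 | 3.4 | 14.7 |
| 10% | 31 | 283 | 3.5 | 10.6 |
| 30% | 94 | 220 | 4.0 | 6.1 |
| 50% | 157 | 157 | 4.7 | 4.7 |
| 70% | 220 | 94 | 6.1 | 4.0 |

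Specificity by type is therefore estimable with reasonable precision over this range. For a rare type, sensitivity is the weaker figure.

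**4. Table 1 against the type aim.** Three types on each method form a 3 × 3 cross-table. One-versus-rest reading gives three sensitivities, three specificities, three PPVs and three NPVs, plus one overall agreement. Table 1 offers one cell per metric for the histogram. In the PBS column, PBS is compared with itself, so every defined accuracy metric is 100% by construction.

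**The case against.** The strongest reply is that the abstract's wording is loose and the real aim is type. Results holds the sentence saying what the study sets out to determine, and it names three types. Data collection procedure and Outcome measures agree with it. The Discussion describes a study of 354 low-hemoglobin samples that reported sensitivity and specificity by type, so an anemic-only sample is a usable design. On that view enrolment is not at fault, and one-versus-rest coding is detail for a fuller document.

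Much of this stands, and it rules out several stronger readings that a reader might infer:

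- *That specificity and NPV have no negatives at all.* This is true only for anemia itself. For type, patients of the other types are valid negatives.
- *That half the planned metrics are undefined, or that NPV lacks a denominator.* Five metrics are listed, and for anemia itself only specificity is necessarily 0/0. The denominator of NPV is the test-negatives, so NPV is defined, and equal to 0, as soon as one patient is missed.
- *That CBC sensitivity is near 100% by construction.* This would require entry to be decided by CBC hemoglobin. The article does not state that rule; it mentions complaints and family history.

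The reply does not remove the point. The abstract states the detection claim as the expected result, and the article nowhere limits it to type. Using PBS as the reference for anemia would not rescue it: the negatives would be anemic patients whose smear was read as not anemic. Nor is the undefined target merely omitted detail, because the article names two targets and Table 1 fixes a layout that does not fit the one that can be estimated.

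**Conclusion.** The concern holds as a mismatch between population and claim, together with an undefined target condition. For anemia present versus absent there are 0 reference-negatives among 314: specificity cannot be estimated, PPV is fixed at 100%, NPV is 0 or 0/0, and accuracy repeats sensitivity. This rests only on the stated entry rule and analysis set.

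The type aim survives. Over assumed type shares from 70% down to 5% there are 94 to 298 negatives per type, and a half-width for specificity of 6.1 to 3.4 points if specificity is 0.90. Those shares and that specificity are assumptions. What is missing for this aim is a statement of what counts as positive and a results table that matches three types.

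**What to change.** - **Statistical analysis:** define positive as the given type on PBS and negative as any other type among the anemic patients. Report histogram/CBC sensitivity, specificity, PPV and NPV for each type, and overall agreement from the cross-table. State where mixed or dimorphic pictures, which the Discussion mentions, are counted. Label PPV and NPV as specific to this hospital's case mix.
- **Table 1:** give the histogram metrics by type. Remove the accuracy metrics from the PBS column, since PBS is the reference. The time and cost rows can stay for both methods.
- **Abstract:** replace the detection wording with *morphological classification in patients with known anemia*.

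**Cost:** one accuracy table per type, with the detection claim and the PBS accuracy column given up. No new patients or tests are needed.

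Keeping the detection claim would instead mean enrolling non-anemic participants. By 1.96² × sp × (1 − sp) / 0.05², a ±5-point interval for specificity (sp) would need 246, 139 or 73 of them at an assumed specificity of 0.80, 0.90 or 0.95.
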